### Quantitative data collection

Quantitative data will be collected from the study participants in S2 and S3 at four different points (t0–t3) through (online) surveys, depicted graphically in figure 3.

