**Figure 3 F3:**
[figure not shown]
Overview of quantitative data collection.

t0 (first survey) transpires when insured persons are confirmed that participation in the prevention intervention is possible.t1 (second survey) takes place at the beginning of the prevention intervention within the first 2 days of the initial inpatient phase.t2 (third survey) is conducted 2 weeks after t1, at the end of the initial inpatient phase.t3 (fourth survey) occurs 12 weeks after the inpatient phase at the end of the 12-week training phase.

The primary outcomes of interest are workability, assessed using the German Work Ability Index^70^; quality of life, using the German WHO Quality of Life-BREF^71 72^; stress levels, evaluated using the Depression Anxiety Stress Scale-21 (DASS-21)^73–75^ and eHealth literacy, which will be assessed using the G-eHEALS^76–78^ and a self-developed instrument for holistic DHL. The secondary outcomes are anxiety and depressive symptoms (DASS-21) and self-efficacy using the SWOP K9.^79–82^ Further information on the validity and reliability of the assessment instruments is provided in ‘online supplemental material 1’. In addition, we are interested in health behaviour as a secondary outcome, which we operationalise as alcohol consumption, smoking, physical activity and dietary behaviour. The training phase behavioural data follow the FITT criteria^83 84^: frequency, intensity, time and type. We will use FITT data to examine participants’ adherence to the eHealth application.^85^ Additionally, sociodemographic data will be collected during survey t1, and behavioural data from the training phase will be gathered during survey t3.

10.1136/bmjopen-2023-081390.supp1Supplementary data

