#### Quantitative analysis

Quantitative data analysis will be conducted using the IBM SPSS software (Version 29.0.1.0). During S2, the dataset will undergo a preliminary examination for meaningfulness. This involves checking for the data’s completeness, outliers and plausibility. A descriptive characterisation of the quantitative S2 sample will be performed based on sociodemographic data to gain initial insights into the sample.

For S3, we plan a pre–post design effectiveness evaluation. The baseline data will be compared with the data from t1 to t3. For this, we will conduct multifactorial variance analyses to investigate whether there are differences in the groups of individual intervention time points regarding the primary and secondary outcomes, thus demonstrating the potential effect of the prevention intervention. Additionally, we will perform regression analyses to interpret the relationship between the collected variables, allowing for statements about the influence of individual variables on different outcomes. Similarly, we present a differentiated sample characterisation for S3. In addition, we add a waitlist-controlled component. After collecting data from t0 to t4, we divide participants of S3 into an intervention and waitlist group. We conduct t-tests within each group to analyse the effects between t0 and t1 for the waitlist group and between t1 and t3 for the intervention group. Calculating Cohen’s d helps us quantify effect sizes from these tests. We then use a Z-test to compare Cohen’s d values of both groups to determine if there are significant differences in effect sizes.

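### The waitlist and intervention groups are formed by dividing S3 participants after outcomes are collected, although every participant is scheduled for both periods; a within-person comparison should replace the division

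*Protocol article*

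**What the plan says.** The component is described in the protocol article under Quantitative analysis: "After collecting data from t0 to t4, we divide participants of S3 into an intervention and waitlist group". The next sentences assign one period to each group: "We conduct t-tests within each group to analyse the effects between t0 and t1 for the waitlist group and between t1 and t3", where the second interval belongs to those labelled as treated. The results are then compared: "We then use a Z-test to compare Cohen’s d values of both groups".

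The schedule under Quantitative data collection is the same for everyone: "Quantitative data will be collected from the study participants in S2 and S3 at four different points (t0–t3) through (online) surveys". The three surveys that matter here are:

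- t0: "t0 (first survey) transpires when insured persons are confirmed that participation in the prevention intervention is possible"
- t1: "t1 (second survey) takes place at the beginning of the prevention intervention within the first 2 days of the initial inpatient phase"
- t3: "t3 (fourth survey) occurs 12 weeks after the inpatient phase at the end of the 12-week training phase"

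The section on the quantitative sample makes taking part in the intervention an inclusion criterion, plans 960 participants for S3, and expects dropout, mainly in the digital training phase.

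**The concern.** A waitlist comparison normally contrasts people who are waiting with other people who are being treated, and membership is settled before outcomes are seen. Here everyone surveyed is an intervention participant who first waits (t0 to t1) and is then treated (t1 to t3). The two groups are a product of the analysis, and the text places their creation after data collection.

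Two things are at stake. The first is precision: each person could supply both changes but is used for only one. The second is protection against outcome-dependent grouping, which a division made after the outcomes exist does not give by itself. The component matters because the rest of the S3 effectiveness analysis is an uncontrolled pre–post comparison. This is the only controlled evidence on whether the intervention succeeds, which is the second key question of stage 3.

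The same sentence also refers to a wave t4 that the survey schedule does not contain.

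**Working it through.** **The plan's own figures.** S2 has 60 participants and S3 has 960, and 60 + 960 = 1020, the total given under The framework of the intervention. No power calculation, split ratio or correlation is stated for this component, so nothing else can be reproduced.

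**Assumptions not in the document.** A 480/480 split, no dropout, equal variance at each wave (set to 1), and between-wave correlation r from 0.4 to 0.8. The pattern is either compound symmetry (the same r for every pair) or AR(1) (r for t0–t1 and t1–t3, r² for t0–t3). Tests are two-sided at 0.05 and power is 80%.

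**Change scores.** D1 = Y(t1) − Y(t0) is the waiting change and D2 = Y(t3) − Y(t1) the intervention change. Each has variance 2(1 − r). Their covariance is r13 − 1 − r03 + r01, which is −(1 − r) under compound symmetry and −(1 − r)² under AR(1).

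**Reading 1: disjoint groups.**

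- Change scores scheduled: 2 × 960 = 1920. Used: 960. Unused: 960, whatever the split ratio.
- Variance with the split: 2(1 − r)/480 + 2(1 − r)/480 = 8(1 − r)/960.
- Variance of the mean of D2 − D1 in all 960 participants: 6(1 − r)/960 under compound symmetry; (1 − r)(6 − 2r)/960 under AR(1).
- Ratio, compound symmetry: 8/6 = 1.33 for any r.
- Ratio, AR(1): 8/(6 − 2r), which is 8/5.2 = 1.54 at r = 0.4 and 8/4.4 = 1.82 at r = 0.8.

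At r = 0.7 with compound symmetry the standard errors are √(1.2/480) = 0.050 SD for the split and √(1.8/960) = 0.043 SD within person. The difference detectable with 80% power is (1.960 + 0.842) × SE. At r = 0.6:

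| Analysis | Variance | SE (SD) | Detectable difference (SD) |
|---|---|---|---|
| Split 480/480 | 1.6/480 = 0.00333 | 0.0577 | 0.162 |
| Within person, compound symmetry | 2.4/960 = 0.00250 | 0.0500 | 0.140 |
| Within person, AR(1) | 1.92/960 = 0.00200 | 0.0447 | 0.125 |

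**Does the division rule matter?** A simulation with no change at any wave (4000 runs, 480/480, compound symmetry with r = 0.6) applied the Z-test on Cohen's d under three illustrative rules, none of them taken from the document:

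| Division rule | Type I error | Mean difference in d (absolute) |
|---|---|---|
| Random | 5.2% | 0.00 |
| Weakly related to the t1 value | 5.0% | 0.00 |
| Weakly related to the t3 value | 35% | 0.10 |

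The t1 rule does no harm because it shifts both groups' changes equally and the shifts cancel. The result depends on the rule.

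**Reading 2: everyone in both groups.** D1 and D2 share the t1 value with opposite signs. Their correlation is −0.5 under compound symmetry and −(1 − r)/2 under AR(1), that is −0.3 to −0.1. A Z-test that ignores this takes the variance as 4(1 − r)/960, which is too small. Under compound symmetry the effective critical value is 1.96 × √(4/6) = 1.60, a true alpha of about 11%. Under AR(1) it is 1.96 × √(4/(6 − 2r)), which gives 8.6% at r = 0.4 and 6.2% at r = 0.8.

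**Period lengths.** From t1 to t3 is about 2 + 12 = 14 weeks. From t0 to t1 has no stated length.

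**The case against.** The strongest reply has four parts.

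- **No harmful rule is stated.** The article is condensed, and the allocation rule may be in a fuller document. A random split drawn at database close would be valid, as the 5.2% shows. This stands. A reader might infer that the comparison is biased, perhaps without limit, or that people lacking a t3 survey will become the waitlist group. The article says neither. What remains is the stated timing, which leaves the possibility open.
- **The split makes the groups independent, as a two-sample Z-test requires, and the cost is only efficiency.** This also stands. The loss is moderate with 960 participants and does not invalidate the study. But it buys nothing that a within-person analysis would not provide.
- **The component is an addition.** The main S3 analysis is pre–post, uses all waves and is untouched by the division. This is correct, and it limits the severity.
- **The raw difference between the two changes has its own weakness.** It sets about 14 weeks against a wait of unstated length, so unequal duration could be mistaken for effect. This is a fair objection to a simple contrast, and the fix must deal with it.

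The division could also be read as a loose way of labelling periods. Then no data are lost, but Reading 2 applies and the Z-test fails instead.

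**Conclusion.** The point holds as a should-fix. Neither reading of the division gives a sound comparison as written. With disjoint groups, half of the scheduled change scores go unused here, and the variance is 1.33 times that of the within-person contrast under compound symmetry and 1.54 to 1.82 times under AR(1). Group membership is also left open to dependence on outcomes. With everyone in both groups, a Z-test that assumes independence has a true alpha of about 6% to 11% instead of 5%.

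These sizes rest on the assumed correlations of 0.4 to 0.8 and on 960 complete cases; the disjoint-group ratios also assume a 1:1 split. Both periods per person holds by schedule only, since dropout will remove some t3 values.

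A reader might go further and conclude that the type I error will be 35%, or that the answer on effectiveness collapses. The documents do not support that: the 35% belongs to one hypothetical rule, and the pre–post analysis remains. The t4 reference is a separate inconsistency in wording and adds no weight to the selection risk.

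**What to change.** 1. Delete the division into groups and the Z-test on Cohen's d.
2. Prespecify a within-person comparison of the t1–t3 change with the t0–t1 change in all S3 participants, estimated from a repeated-measures mixed model and reported with a 95% confidence interval.
3. Include actual elapsed time between surveys in that model, and state how the waiting-period change is set against the roughly 14 weeks from t1 to t3.
4. Describe the result as a within-person waiting-period comparison, not as a randomised waitlist effect.
5. If separate groups are kept for any reason, fix membership by a computer-generated random split before any S3 outcome is read.
6. Reconcile t4 with the four surveys t0 to t3.

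The cost is analysis wording. No extra participants or surveys are needed; the dates of the t0, t1 and t3 surveys must be available for the elapsed-time term.

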##### Quantitative sample: participants of the intervention (S2, S3)

We aim to survey all participants from the intervention’s piloting (S2) and evaluation (S3) stages. We will use a non-probability sample for recruitment. Participants in the prevention intervention will receive a flyer on recruitment for our study via the German Pension Insurance and the intervention clinics. On the flyer are instructions and online access for our quantitative data collection. In S2, we expect a total of 60 participants. In S3, we intend to include 960 participants for the pre–post design effectiveness assessment. Inclusion criteria are the participation in the prevention intervention and sufficient German language skills. We expect drop-outs, especially during the digital training phase.

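### The only waitlist comparison described is a Z-test on two within-group Cohen's d values with no common standardiser, so equal non-zero changes can test as different and real differences can be hidden

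*Protocol article*

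**What the plan says.** All of this is in the protocol article under Quantitative analysis. The main evaluation in stage 3 is pre–post: "For S3, we plan a pre–post design effectiveness evaluation", using multifactorial variance analyses across the survey time points. A second element follows: "In addition, we add a waitlist-controlled component". For it, "we divide participants of S3 into an intervention and waitlist group", and t-tests are run within each group "to analyse the effects between t0 and t1 for the waitlist group and between t1 and t3 for the intervention group". Then: "Calculating Cohen’s d helps us quantify effect sizes from these tests". The comparison between the groups is the last step: "We then use a Z-test to compare Cohen’s d values of both groups to determine if there are significant differences in effect sizes".

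The article does not say which SD goes into d, or which variance formula goes into the Z-test. It describes no other comparison with the waitlist group. The two intervals differ. Under Quantitative data collection, t1 to t3 covers the 2-week inpatient phase and the 12-week training phase, about 14 weeks. The waitlist interval starts at t0, which "transpires when insured persons are confirmed that participation in the prevention intervention is possible", and ends at the start of the inpatient phase. The text does not fix its length. The planned sample is given under Quantitative sample: "In S3, we intend to include 960 participants for the pre–post design effectiveness assessment".

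**The concern.** A d taken from a paired t-test is the mean change divided by the SD of change. That SD gets smaller as the correlation between the two waves rises. One group is followed through an untreated wait of unstated length and the other through about 14 weeks that contain the treatment, so equal correlations cannot be taken for granted. The Z-test then asks whether two ratios differ, not whether the groups changed by different amounts on the WAI, the WHOQOL-BREF or the DASS-21.

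The waitlist component is the only part of the described plan that could separate the intervention's effect from change that would have happened anyway. If its test responds to differences in correlation, it can signal a difference where the mean changes are the same or miss one that exists. Its result also cannot be read in scale points.

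**Working it through.** The article gives no alpha, power, effect size, SD or wave correlation for this component, so there is no stated figure to reproduce. The check asks how the described test behaves when both groups have the same true mean change.

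**Inputs**
- From the article: 960 participants in stage 3; waitlist interval t0 to t1; intervention interval t1 to t3.
- Assumed: a 480:480 split (240:240 as a low case, since drop-out is expected but not quantified); independent groups; two-sided 5% level; equal raw SDs, set to 1; wave correlations r of 0.8 for t0 to t1 and 0.6 for t1 to t3; mean change m in units of the raw SD.

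**Formulas**
- SD of change = √(2(1 − r)): √0.4 = 0.632 for the waitlist, √0.8 = 0.894 for the intervention.
- d = m / SD of change, with Var(d) = (1 + d²/2)/n.
- Z = (d_waitlist − d_intervention) / √(sum of the two variances).

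**Worked case, m = 0.3 in both groups**
- d = 0.3/0.632 = 0.474 and 0.3/0.894 = 0.335.
- Variances: (1 + 0.1125)/480 = 0.00232 and (1 + 0.0563)/480 = 0.00220. The standard error is √0.00452 = 0.067.
- Z = 0.139/0.067 = 2.07. The test is expected to land beyond 1.96 although the changes are equal.

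| Equal change m (SD) | d waitlist | d intervention | Expected Z | Rejection, n = 480 | Rejection, n = 240 |
|---|---|---|---|---|---|
| 0 | 0 | 0 | 0 | 5% | 5% |
| 0.1 | 0.158 | 0.112 | 0.71 | 11% | 8% |
| 0.2 | 0.316 | 0.224 | 1.41 | 29% | 17% |
| 0.3 | 0.474 | 0.335 | 2.07 | 54% | 31% |
| 0.5 | 0.791 | 0.559 | 3.23 | 90% | 63% |

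Expected Z is for n = 480. Simulation agrees with the formula to within about two percentage points. In the same simulations a direct test of the difference in mean change rejects about 5% of the time in every row.

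**Other correlations** (m = 0.4, n = 480): 0.7 and 0.6 give 17%; 0.7 and 0.5 give 40%; 0.8 and 0.5 give 92%. Equal correlations give 5%.

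**Direction.** With the higher correlation in the waiting interval, the waitlist d is the larger one, so the excess rejections favour the waitlist. With the correlations exchanged, they favour the intervention at the same rate (about 29% at m = 0.2).

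**Masking.** Take true changes of 0.25 SD (waitlist, r = 0.8) and 0.395 SD (intervention, r = 0.5). Then d = 0.25/0.632 = 0.395 and 0.395/1 = 0.395. The Z-test on d rejects about 5% of the time; the direct test of mean change rejects about 76%.

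**If d uses a raw SD instead**
- With the independent-sample variance, (2 + d²/2)/n, the pairing is ignored and rejection under equal change is about 0.1% or less. The test is far too conservative.
- With a variance that respects the pairing, (2(1 − r) + d²/2)/n, rejection is about 5% when the groups' baseline SDs are equal. When they differ by a ratio of 1.1, 1.2 or 1.3, it is 10%, 22% or 37% (m = 0.4, r = 0.7 and 0.6, n = 480).

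**The case against.** Four objections have weight.

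First, a reader might infer that this Z-test decides whether the intervention works. The article does not support that. It places the effectiveness evaluation in the pre–post variance analyses, its abstract names only those, and the waitlist component is an addition. What stands is that the Z-test is the only comparison with the waitlist that is described.

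Second, the standardiser is not named, and a condensed article may leave it to a fuller document. Scaling by each group's own SD of change is an inference from d being calculated from the t-tests, not a stated rule. What the article does fix is that the two d values are the quantities compared.

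Third, a reader might infer that the error rate is wrong however d is built. That is not so: a raw-SD d with a paired variance holds its level when baseline SDs are equal.

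Fourth, a reader might take the rejection rates as false claims of benefit. In the case tabulated they run the other way, and the cost to the intervention is lost power. For true changes of 0.1 SD (waitlist) and 0.3 SD (intervention), the Z-test on d detects the difference about 78% of the time and the direct test about 98%. The larger rates also require the untreated group to improve as much as the treated one. At an equal drift of 0.1 SD, rejection is about 11%.

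The research questions ask for the effect on each named instrument without requiring a contrast in raw points. Preferring scale points is partly a matter of judgement. The test's dependence on the wave correlation is not.

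**Conclusion.** The concern holds for the added waitlist comparison. As described, it tests two within-group effect sizes from different intervals with no common standardiser. On the natural reading, its rejection rate under equal non-zero changes rises from about 11% at 0.1 SD to about 90% at 0.5 SD, and it can miss a real difference that a direct test would usually find.

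These sizes rest on assumed correlations, an assumed 480:480 split and an assumed 5% level; smaller groups or closer correlations reduce them. The distortion disappears if neither group changes or if the SDs of change are equal. Its direction depends on which interval has the higher correlation, which the article gives no means of knowing. It does not follow that the main pre–post analysis is affected, or that every way of building d fails.

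**What to change.** Replace the Z-test on the two d values with a direct contrast between the groups: mean change from t1 to t3 in the intervention group minus mean change from t0 to t1 in the waitlist group, on each instrument's original scale, with a 95% CI and a standard error that allows unequal SDs of change. Report Cohen's d only as a description, dividing both changes by one common SD, such as the t1 SD of all stage 3 participants, and name that denominator.

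The cost is about one sentence of analysis wording, settled before the stage 3 data are analysed. No additional data, visits or participants are needed. The change corrects the test statistic only; it does not make the two groups or their intervals comparable.

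### The Z-test sets two groups against each other although every participant is scheduled for both intervals: if people overlap, its error rate is not secured, and if they do not, half of the change scores go unused

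*Protocol article*

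**What the plan says.** All statements are in the protocol article.

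- **Groups.** Under Quantitative analysis, once the survey data are in, "we divide participants of S3 into an intervention and waitlist group". No allocation rule is given.
- **Contrasts.** Within-group t-tests are run "to analyse the effects between t0 and t1 for the waitlist group and between t1 and t3 for the intervention group", and each is expressed as Cohen's d.
- **Comparison.** "We then use a Z-test to compare" the two groups' d values, to see whether the effect sizes differ significantly. The article gives no standard error, no standardiser for d and no significance level.
- **Schedule.** Under Quantitative data collection, stage 2 and stage 3 participants are surveyed at t0, t1, t2 and t3. Survey t0 follows confirmation that participation is possible. Survey t1 "takes place at the beginning of the prevention intervention within the first 2 days of the initial inpatient phase". Survey t3 comes at the end of the 12-week training phase.
- **Who is in the sample.** Under the quantitative sample, taking part in the intervention is an inclusion criterion, and 960 people are intended for stage 3. No one is enrolled as an untreated control.

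**The concern.** The labels waitlist and intervention correspond to two successive intervals that each participant passes through, with t1 closing one and opening the other. Nothing in the schedule separates people into those who wait and those who are treated, so one person can supply both t1-t0 and t3-t1. These two changes contain the same t1 score with opposite signs and will usually be negatively correlated. A Z-test for two separate groups has no term for that correlation.

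At stake is the part of the stage 3 evaluation that the plan presents as waitlist-controlled. If its standard error is wrong, a significant difference in effect sizes does not carry the error rate a reader would assume. If the groups are kept apart instead, the test is sound on this count but uses only one of the two changes each person provides.

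**Working it through.** The plan states no level, standard error or error rate for this test, so there is no figure of its own to reproduce.

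**Assumptions.** Two-sided 5% level; equal numbers in both groups; unit variances at t0, t1 and t3; a share f of people in both groups, from 0 to 1. The correlations r01, r13 and r03 between surveys are not in the article and are varied below. Both d values use the SD of change, and the Z-test adds their variances.

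**Covariance of the two changes**

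- Var(t1-t0) = 2(1-r01)
- Var(t3-t1) = 2(1-r13)
- Cov = r01 + r13 - r03 - 1
- ρ = Cov / √(Var·Var)

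**Error rate.** For d values near zero, the Z-test's variance is proportional to 2 and the true variance to 2 - 2fρ. The true standard error is therefore √(1-fρ) times the assumed one, and the actual error is 2[1 - Φ(1.96/√(1-fρ))].

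| r01, r13, r03 | Variances | Cov | ρ | Error, f = 1 | Error, f = 0.5 |
|---|---|---|---|---|---|
| 0.6, 0.6, 0.6 | 0.8, 0.8 | -0.4 | -0.50 | 11.0% | 8.0% |
| 0.7, 0.6, 0.5 | 0.6, 0.8 | -0.2 | -0.29 | 8.4% | 6.7% |
| 0.8, 0.6, 0.5 | 0.4, 0.8 | -0.1 | -0.18 | 7.1% | 6.0% |

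- In the first row the standard error ratio is √1.5 = 1.22. Any common correlation gives the same ρ = -0.5.
- At ρ = -0.5, overlap of 75, 50, 25 and 0% gives 9.5, 8.0, 6.5 and 5.0%.
- With full overlap and first-order autoregressive correlations of 0.3, 0.5, 0.7 and 0.9, ρ = -(1-r)/2 and the error is 9.2, 8.0, 6.8 and 5.6%.
- Simulation (8,000 runs each, n = 960, common correlation 0.6) gave 10.95% with the same people in both groups and 4.4% with two disjoint halves.

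**Where the direction reverses**

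- If the two changes were positively correlated at 0.25, the error with full overlap would be 2.4%.
- Suppose d uses the raw-score SD with an independent-groups standard error. Under full overlap and common correlation r, the assumed variance is 4/n and the true variance is 4(1-r)/n + 2(1-r)/n = 6(1-r)/n. The two are equal at r = 1/3. The error is 7.4% at r = 0.2, 2.4% at r = 0.5 and 0.35% at r = 0.7.

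**What disjoint groups cost.** Write V1 and V2 for the variances and C for the covariance. Splitting n people into halves gives a difference in mean change with variance 2(V1+V2)/n. Using both changes from all n gives (V1+V2-2C)/n. The ratios for the three rows are:

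- 2.4/3.2 = 0.75
- 1.8/2.8 = 0.64
- 1.4/2.4 = 0.58

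The within-person variance is thus 25 to 42% lower, despite the negative covariance.

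**The case against.** The strongest reply is that the text describes dividing participants into two groups, testing within each, and comparing the two. Ordinarily that puts each person in one group only. Different people then supply each d, the shared t1 time point creates no covariance between them, and the error is the nominal 5%. This stands. That everyone has t0, t1 and t3 makes overlap possible; it does not show that anyone is used twice.

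It is also fair that the division rule and the standard error may be in a fuller protocol or analysis plan. Their absence from an article is not the finding. What remains is the stated choice: a two-group comparison of intervals that each participant supplies in full.

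A reader might infer that the plan assumes independence, that its standard error is therefore too small, and that the error is 11%. The article does not support this. It states neither independence nor a standard error, and the direction depends on the standardiser and the covariance structure. The 11% is one scenario and not an upper bound (the formula reaches 16.6% at the limit ρ = -1).

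Finally, the component is introduced as an addition to the pre-post variance analyses. If their baseline is t0, those analyses also span the waiting interval. It would be too strong to say that the whole evaluation rests on this test.

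**Conclusion.** The point holds in conditional form, and the change is worth making before analysis.

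- **If people enter both groups,** a Z-test that adds the variances is not valid. Its error would be about 6 to 11% under common correlation patterns. This rests on change-score standardisation, an independence standard error and a two-sided 5% level, all of them assumptions. Other choices can take it below 5%.
- **If the groups are disjoint,** the error rate is sound. The test then leaves one usable change per person unused, has a larger variance than the within-person comparison under the correlations assumed, and gives a result that depends on a split made after data collection.

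On either reading, a within-person comparison fits the schedule better than the stated test.

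**What to change.** Replace the two-group Z-test with a within-person comparison in all stage 3 participants who have t0, t1 and t3: the mean of (t3-t1)-(t1-t0), with its own standard error and confidence interval.

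If a difference between d values is wanted, resample persons with a bootstrap, recompute both d values and their difference each time, and take the interval from that distribution. This is a related but not identical estimand: the first is a difference in raw mean change, the second a difference in standardised change.

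If disjoint groups are kept, say that they are disjoint and how they are formed. No replacement is then needed to protect the error rate.

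The cost is a sentence or two in the analysis section and a short script, with no new data. If the groups would have overlapped, the interval may be wider than the naive one. The contrast needs all three surveys, so the drop-out the article expects in the training phase will reduce the number analysed. The change corrects the standard error and uses the data fully; it does not make the comparison of two successive periods a randomised one.
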